### Process evaluation

The process evaluation will explore and assess factors influencing the delivery of the intervention and provide important context for interpreting the trial results. It will examine the credibility and acceptability of the intervention, gathering patient participants’ views on their satisfaction with the care they received, the perceived impact on outcomes and their experiences of taking part in the trial. It will also capture physiotherapists’ perspectives on delivering the guided consultation, including their views on the intervention’s effectiveness and its impact on their approach to shoulder pain management. These qualitative data will help identify key factors shaping the intervention’s delivery and outcomes. A multimethod approach will be used which will include semistructured interviews with participants and physiotherapists, audio-recording of the guided consultation, analysis of data collected during the consultation using CRFs, and participant questionnaires.

#### Semistructured interviews

Semistructured interviews focusing on how the intervention is used and understood and guided by the elements and principles underpinning the intervention will be carried out with patient participants and physiotherapists:

Patient participants (up to n=20) will be selected to represent different prognostic profiles, ages, genders, work statuses and geographic areas. A sample of these interviews will be conducted in the first 6 months of recruitment to help interpret results from the internal pilot phase and refine the intervention or trial processes, such as refinements to physiotherapist training. Interview topics will cover experience of recruitment, questionnaire completion, views on discussions about shoulder pain diagnosis, prognosis and management of shoulder pain during consultations, perceptions of advice given, how decisions were made, reassurance provided, and overall confidence to manage shoulder pain and satisfaction with their treatment.Interviews with physiotherapists (approx. n=10) will focus on their views regarding the content and usefulness of training materials, changes in confidence in managing shoulder pain, assessing and discussing prognosis and providing reassurance. Their views on perceived barriers and facilitators to delivering the guided consultation will also be explored.

Patient participants who agree to be contacted for an interview in their baseline questionnaire will be sampled to ensure variation in characteristics such as reported pain severity, ethnicity, age, gender, work status and geographic location (across different physiotherapy services). Patients will receive an invitation letter and information leaflet detailing the interview purpose and information about confidentiality, data storage and archiving. A reply slip will also be included for them to return to indicate interest and provide contact details. A research team member will then contact the participant to schedule the interview (eg, either by phone or videoconference). Before the interview, verbal consent will be audio-recorded with consent reaffirmed at the end.

Physiotherapists will be invited to participate in interviews as part of their involvement in the trial, with sampling based on gender, work location and years of clinical experience. They will receive an interview invitation and information leaflet by email. A research team member will contact them to arrange the interview, which will take place using either phone or video call. Consent will be obtained in the same manner as for patients.

The final number of interviews will be guided by inductive thematic saturation, where data collection stops once no new themes or codes are identified.^41^ The semistructured interviews will allow the interviewer, trained in qualitative methods, to explore additional relevant topics as they arise. The topic guides will be revised iteratively during data collection and analysis based on ongoing findings.

#### Audio-recording of consultations

Up to 10 guided consultations will be recorded to assess the use of the three components of the intervention, specifically whether it is delivered according to protocol, including effective reassurance, personalised self-management advice and treatment based on the individual needs of the patient and their estimated prognosis.

Patient participants who agree to be contacted for consultation recordings in their baseline questionnaire will be selected using the same criteria as for the semistructured interviews. These participants will receive an invitation letter, information leaflet and consent form. For those participants who consent to their consultation being recorded, the research team will liaise with the physiotherapy service to confirm the date of the consultation. The physiotherapist, who will also complete a consent form, will be informed. Both participant and physiotherapist consent will be obtained before the consultation is recorded.

The physiotherapist will reaffirm the patient’s consent and use a secure, password-protected digital recorder to record the consultation. Afterwards, the recording will be couriered to Keele CTU for upload to a secure SharePoint location, and the original file will be deleted. If consent is not provided or is withdrawn, or a suitable room is unavailable, the consultation will not be recorded.

#### Data collected during the personalised guided consultation

Descriptive analysis of the CRFs, consultation summary and patient questionnaires will provide quantitative data on the following: uptake of the intervention by physiotherapists, consultation duration and the extent to which treatment and self-management options align with patients’ expressed needs, prognostic factors and predicted future levels of shoulder pain and disability. The patient questionnaires (at baseline, 6 weeks and 6 months) will also capture data on potential mediators (reassurance, worry, self-efficacy and shared decision-making), helping to explore how these factors may influence the intervention’s impact on patient outcomes.

### Internal pilot

The internal pilot will aim to assess recruitment, retention and intervention uptake, test trial procedures and explore intervention acceptability. It will form the first phase of the main trial recruiting at least 200 participants from 4 to 6 physiotherapy services over 6 months. Recruitment will not be stopped at the end of the internal pilot period, but there will be the opportunity, while recruitment is ongoing, to potentially revise trial procedures for the main trial. To improve intervention uptake, actions may include identifying barriers to adoption with physiotherapists, revising training materials and offering refresher courses, providing mentorship and supervision from senior team members. A priori defined success criteria will be used to assess progress during the internal pilot phase (see table 2). These criteria are similar to stop/go criteria, but their purpose is to inform discussions with the Programme Steering Committee (PSC—see Trial monitoring).

**Table 2 T2:** A priori defined criteria to assess progress during the internal pilot phase of the PANDA-S trial

	**Continue as planned**	Implement remedies and continue, with protocol amendments as needed	Discuss the feasibility of continuing with the Programme Steering Committee
Recruitment	≥80% of the target participants by 6 months (n≥160)	≥50%, <80% of the target participants by 6 months	<50% of the target participants by 6 months
Follow-up rate (6 weeks*)*	≥70% retention	≥50%, <70% retention	<50% retention
Risk of participation bias (baseline similarity)	<15% difference in participant characteristics	>15% difference in participant characteristics	–

PANDA-S, Prognostic And Diagnostic Assessment of Shoulder Pain.

### Analysis

Data will be reported according to the reporting guidelines for randomised clinical trials: Consolidated Standards of Reporting Trials (CONSORT 2010) statement^42 43^ including extensions to cluster randomised trials^44^ and pragmatic trials.^45^ A CONSORT style flow diagram will be used to show the flow of participants through the trial, including reasons (where given) for withdrawal at both the physiotherapy service and individual participant level. These will be recorded on REDCap. Analysis will be conducted by a statistician who will remain blind to the allocation of physiotherapy clusters to either intervention or control arm.

#### Internal pilot analysis

Data from the internal pilot phase will be analysed using descriptive methods.

#### Sample size calculation

The sample size for the trial is based on previous studies using the SPADI^18 46^ and using data from the PANDA-S cohort study.^32^ The trial aims for 90% power to test the superiority of the intervention to usual care by physiotherapists for patients with shoulder pain. The calculations assume a 5% type I error (two-tailed) and aim to detect an effect size of 0.30 (8–10 point difference, SD 24–30) in the primary outcome.^47^ The calculation takes into account the clustering of individual participants by service (ICC 0.02)^48^ and likely loss to follow-up of 25% over the 12 month follow-up (inflationary effect on the sample size), repeated measurements^49^ and adjustment for baseline SPADI scores (deflationary effect). To achieve this, 416 participants per arm, or 832 in total, are required.

#### Main trial analysis

Baseline characteristics of the physiotherapy service clusters, and individual participants will be described for each trial arm. This includes the primary outcome, secondary outcomes, process measures, predicted SPADI scores and the proportion of participants predicted to score 20 or lower on the SPADI, indicating recovery.

The primary intention-to-treat (ITT) analysis will use a hierarchical linear mixed regression model to compare offering the intervention with usual care on SPADI total scores over the 12 months follow-up. This model will account for repeated measures within individuals and clustering within physiotherapy services, using available data from all time points and assuming missing data are random. Analyses will adjust for baseline SPADI score, age, sex and physiotherapy cluster size. A non-responder analysis will assess the risk of attrition bias. Data for individuals who withdraw consent will be included up to the point of withdrawal.

We will report mean differences and standardised effect sizes (relative to the overall SD) for the primary outcome. The number (percentage) of participants in each trial arm scoring 20 or lower on the SPADI at 6 and 12 months follow-up will also be reported, which will be used to calculate the Number-Needed-to-Treat.

The model parameters will primarily be estimated using maximum likelihood estimation (MLE). To address potential issues due to the small number of clusters, restricted maximum likelihood estimation (RMLE) will also be used as a sensitivity analysis. This will include evaluations with and without the Kenward-Roger approximation correction^50^ for SE and df in estimating fixed effects.

Analysis of secondary outcomes will be carried out using an ITT approach, using a linear mixed model for numerical outcomes and generalised mixed logistic models for categorical outcomes. The models will be adjusted for baseline SPADI, age and sex (participant-level) and physiotherapy service cluster size. A sensitivity analysis will be considered if there is baseline imbalance between arms, with additional adjustment for baseline characteristics that are >10% different for categorical variables, or >2 times the SE for numerical variables. For work absence, performance and healthcare utilisation, the analysis will focus on 6 and 12 month follow-up data, as these measures are not collected at the 6 week follow-up.

Sensitivity analyses will be carried out to provide an unbiased estimate of intervention effect for participants who received the guided consultation as per protocol. Exploratory subgroup analyses will be conducted for the primary outcome to explore the effectiveness of the intervention. These analyses will be carried out in participants with (1) long (> 6 months) versus short baseline pain duration; (2) having received previous treatment for their shoulder condition, or not; (3) low versus increased levels of distress (symptoms of anxiety and depression) and (4) those living in areas with low versus high deprivation.

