**Trial registration number:**

ISRCTN45377604.

STRENGTHS AND LIMITATIONS OF THIS STUDYThis large cluster randomised controlled trial will evaluate the effects and costs of a new intervention, comprising a scalable physiotherapy training package and a personalised guided consultation that incorporates a new prognostic tool, to improve care for patients with shoulder pain in physiotherapy services.A multimethod process evaluation, informed by a predefined logic model, will assess the uptake, acceptability and delivery of the intervention. This approach will allow for a comprehensive understanding of the perspectives and experiences of both participants and physiotherapists.The first phase will be an internal pilot designed to strengthen the trial by assessing recruitment, retention and intervention uptake, increasing the likelihood of successfully delivering the full trial.A potential limitation of the cluster trial design is the increased risk of participation bias related to differential recruitment between trial arms.

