### Randomisation

In line with a cluster RCT design, the NHS physiotherapy services will be the unit of randomisation. As the number of clusters will be small (envisaged to be up to eight clusters per arm), we will use block randomisation stratified by the size of the physiotherapy service, based on the average number of patients treated for shoulder pain (large sites≥150 per month, small sites<150 per month). We will use block sizes of 2 within each stratum to randomly allocate the physiotherapy services to the intervention or control arms. The randomisation sequence will be computer generated using *blockrand* in R.^21^

To minimise the risk of participation bias, all participants will receive the same PIS which informs participants that the study is looking at how the discussion between patients and physiotherapists can best be supported. The PIS does not refer to the trial having two arms (intervention and control). Participants will be asked to consent to participating in a study investigating the delivery of care for shoulder pain by physiotherapists, consisting of the completion of self-report questionnaires (over a period of 12 months). Participants will be informed that they can withdraw from the study at any time without giving a reason, and that a decision to withdraw will not affect their current or future healthcare.

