### Trial intervention

We combined best practice guidance^36^ with the results from a qualitative interview study^8^ and a series of workshops involving patient contributors and clinical advisors to codesign and develop the intervention (the personalised guided consultation and associated training package for Physiotherapists) informed by the Medical Research Council (MRC) framework for complex interventions.^37^ The guided consultation is based on the principles of shared decision-making,^38^ to include effective reassurance, building confidence (self-efficacy) and provision of personalised advice and treatment, and comprises the following three elements:

*Preconsultationform* will be sent to participants in advance of the consultation (with the baseline questionnaire) on which they can highlight their concerns and priorities about their shoulder pain and expectations for the consultation.*Asemistructuredassessment* to guide physiotherapists in covering key elements of the consultation:Subjective examination, which will include an assessment of items for the prognostic tool; an assessment of ideas, concerns and expectations (ICE)^39 40^ as highlighted by participants on the preconsultation form; an assessment of personal values in terms of their shoulder pain and disability.Standardised physical examination, as per usual carePersonalised discussion of expected course of shoulder pain and disability, based on individualised results of the prognostic tool and personal valuesDiscussion of treatment and self-management options, tailored to the identified concerns, priorities, expectations, values, results of physical examination and individual prognosis.The prognostic tool included the items with prognostic value collected in the baseline questionnaire and allows an individualised prediction of the level of pain and disability (SPADI score) at 3 and 6 months displayed as a bar chart.*Aconsultationsummary* will be jointly completed by the participant and physiotherapist to support shared decision-making. The summary will outline shared decisions regarding treatment and self-management options, for the patient to keep for reference following the consultation.

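### The primary model leaves out predicted SPADI from the programme's own prognostic tool, a cheap baseline covariate planned for both arms: a missed gain in precision and robustness, not an error

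*Protocol article*

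**What the plan says.** Under Main trial analysis, the primary intention-to-treat analysis is a hierarchical linear mixed model for SPADI over 12 months, and "Analyses will adjust for baseline SPADI score, age, sex and physiotherapy cluster size". The list is closed.

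The opening paragraph of that section promises a baseline description of clusters and participants by arm: "individual participants will be described for each trial arm". It covers "predicted SPADI scores and the proportion of participants predicted to score 20 or lower on the SPADI, indicating recovery".

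Under Trial intervention: "The prognostic tool included the items with prognostic value collected in the baseline questionnaire", and the tool "allows an individualised prediction of the level of pain and disability (SPADI score) at 3 and 6 months". The Introduction says it was developed within the same research programme. Both arms complete the baseline questionnaire (Recruitment; Table 1).

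On the risk of imbalance, the strengths and limitations box names an "increased risk of participation bias related to differential recruitment between trial arms". Further covariate adjustment appears once in Main trial analysis, in the paragraph on secondary outcomes. It is a sensitivity analysis to be considered if baseline characteristics differ by more than set thresholds. Whether it covers the primary outcome is not clear.

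Randomisation is "stratified by the size of the physiotherapy service, based on the average number of patients treated for shoulder pain", with a cut at 150 per month.

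**The concern.** A single prognostic score for SPADI, defined before the trial's outcome data exist and built from questions put to every participant, is an obvious candidate covariate. Here it is only tabulated.

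Two features of the design make this worth raising. First, there are only 16 services, so chance differences in case mix between arms can be appreciable. Second, participants are identified and consented after their service has been allocated (the intervention arm's study pack already differs, because it holds the preconsultation form), so recruitment itself can create prognostic differences. Baseline SPADI, age and sex cover part of this. The baseline questionnaire also collects pain duration, history, psychological factors and general health, and the tool draws on those items that carry prognostic value.

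At stake are some precision, and some protection against imbalance that would otherwise depend on a rule triggered by the observed data.

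**Working it through.** **Inputs from the article.** Effect 0.30 SD (8–10 points, SD 24–30), two-sided 5%, 90% power, ICC 0.02, 25% loss, 416 per arm, 16 services 1:1. That is 8 services per arm, 416/8 = 52 enrolled per service, 52 × 0.75 = 39 responders per service and 312 per arm.

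**Not in the article (assumed).** The share of outcome variance that the score explains beyond the present covariates: 5–10%. An ICC for the score: 0.02–0.05.

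**1. The stated sample size.** Unclustered: 2 × (1.960 + 1.282)² / 0.30² = 233.5, so 234 per arm.
- With 39 per service: design effect 1 + 38 × 0.02 = 1.76; 234 × 1.76 / 0.75 = 549. The stated 416 implies a deflation of 416/549 = 0.76.
- With 52 per service: design effect 2.02; 234 × 2.02 / 0.75 = 630; implied deflation 0.66.

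The correlations behind the deflation are not given. Plausible ones come close: a single time point with baseline correlation 0.5 gives 549 × 0.75 = 412. So 416 is plausible, though not uniquely reproducible, and it owes nothing to the prognostic score.

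**2. Precision.** The variance per arm mean that gives 90% power (normal reference) is 0.30² / (2 × 3.2415²) = 0.00428. The cluster part is 0.02/8 = 0.0025, leaving 0.00178 for the individual part. With 312 responders the individual variance factor is 0.00178 × 312 / 0.98, about 0.568.

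Let the score explain a further 5% or 10% within services and nothing between them:
- 5%: 0.0025 + (0.568 − 0.05) × 0.98/312 = 0.00413; variance ratio 0.963.
- 10%: 0.0025 + (0.568 − 0.10) × 0.98/312 = 0.00397; variance ratio 0.927.

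Power uses a t reference with 13 df (16 services less intercept, arm and size stratum) and noncentrality 3.2415/√ratio:

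| Added variance explained | Variance ratio | Power |
|---|---|---|
| 0 | 1.000 | 0.850 |
| 5% | 0.963 | 0.862 |
| 10% | 0.927 | 0.875 |

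The gain is 1.3 to 2.5 points. As a cross-check, start from 90% with a normal reference and let the score remove 5–10% of the *residual* variance: power becomes 90.8–91.6% if only the within-service part falls, and 91.4–92.7% if both parts fall in proportion. That is a gain of 0.8–2.7 points, so about 1–3 points either way.

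**3. Imbalance.** The SE of a baseline arm difference, in SD units, is √(2/416 × (1 + 51 × ICC)): 0.099 at ICC 0.02 and 0.131 at ICC 0.05. Apply this to the part of the score not explained by the present covariates, scaled to SD 1. If that part explains a share p of outcome variance, its slope is √p outcome SDs, and the shift is 1.96 × SE × √p:

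| ICC | p | Shift (SD) | Share of 0.30 |
|---|---|---|---|
| 0.02 | 5% | 0.043 | 14% |
| 0.02 | 10% | 0.061 | 20% |
| 0.05 | 5% | 0.057 | 19% |
| 0.05 | 10% | 0.081 | 27% |

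In SPADI points this runs from 0.043 × 24 = 1.0 to 0.081 × 30 = 2.4.

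**The case against.** The strongest reply is that this is a preference. The covariates are named in advance, they include the outcome's own baseline value, and the model is valid. That stands. A reader might infer that leaving the score out undermines the primary analysis or the 90% power. It does not, because the sample size counts only on baseline SPADI and repeated measures.

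It also stands that the tool predicts 3 and 6 months, while the trial measures SPADI at 6 weeks, 6 months and 12 months. Only the 6-month point matches. The article reports no performance figures for the tool, and the score probably overlaps with baseline SPADI, so its added value is unknown. Overlap does not bias the treatment estimate, but it limits the gain.

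A larger power gain is tempting. If the score also removed 20% of between-service variance, power would be 0.902–0.914, a gain of 5–6 points. Nothing in the article supports that figure, least of all alongside a base case in which baseline SPADI, age, sex and size remove none of that variance.

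A larger imbalance effect, up to about a third of the target, would follow from multiplying a partial slope by the raw imbalance in the score. Only the imbalance left after the present covariates counts. As a chance event, 1.96 SE is a 1-in-20 occurrence that the standard error already reflects. Imbalance from differential recruitment is not covered in that way.

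Finally, protection is not absent. There are the existing covariates, a common information sheet that does not mention two arms, a baseline-similarity criterion in the internal pilot and the conditional sensitivity analysis. These lessen the need for the score without replacing pre-specified adjustment.

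**Conclusion.** The point holds as a missed, inexpensive improvement. The primary model is valid, but it leaves out a prognostic score that the trial itself plans to describe in both arms, in a design with few services and recruitment after allocation.

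The size is modest: about 1–3 power points, and a possible shift of about 14–27% of the target effect under a 1.96-SE residual imbalance. Both rest on the assumed 5–10% of added variance explained, and the second also on an ICC for the score of 0.02–0.05. The article does not supply these figures.

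The name of the size covariate is a minor matter. A reader might take cluster size to mean the number recruited, which arises after allocation and could depend on arm. The article does not say so: Settings and clusters defines the cluster as a physiotherapy service, and Randomisation stratifies by service size, so service size is the natural reading.

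**What to change.** Before unblinding, add predicted 6-month SPADI to the primary covariates, alongside baseline SPADI, age, sex and service size. Calculate it the same way in both arms, from the baseline questionnaire only and not from items recorded in the consultation. Fill missing tool items by a simple imputation that ignores arm. Keep the present model as a pre-specified sensitivity analysis. If the team prefers to leave the primary model unchanged, the minimum is to make the score-adjusted model an unconditional sensitivity analysis of the primary outcome.

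As a clarification, name the size covariate as the randomisation stratum (150 or more against fewer than 150 shoulder patients per month).

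The cost is an amended covariate sentence, one participant-level parameter and a missing-item rule. No new data are needed.

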### Inclusion criteria

People referred or self-referred to participating physiotherapy services, aged 18 years or over presenting with shoulder pain will be invited to participate.

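### The NNT is taken from unadjusted arm percentages, so with 16 services it can drift from the adjusted primary result (minor)

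*Protocol article*

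**What the plan says.** All of this is in the protocol article, mostly under Analysis, Main trial analysis.

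- **NNT.** The plan is to give, for each arm, the count and percentage "scoring 20 or lower on the SPADI at 6 and 12 months follow-up". Of these figures the article then says: "which will be used to calculate the Number-Needed-to-Treat". No model, covariate or interval is named for this step.
- **Primary outcome.** "This model will account for repeated measures within individuals and clustering within physiotherapy services", and "Analyses will adjust for baseline SPADI score, age, sex and physiotherapy cluster size".
- **Secondary outcomes.** Categorical ones get mixed logistic models, adjusted for baseline SPADI, age, sex and service size. SPADI of 20 or lower is not listed as a secondary outcome in Table 1 or in the Data collection text, so these models do not clearly reach it.
- **Design.** Sixteen services are randomised 1:1, stratified by service size only (Randomisation). The strengths and limitations box acknowledges a risk of participation bias through differential recruitment between arms.

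**The concern.** An NNT is the reciprocal of a risk difference, so it is an estimate of treatment effect and not just a description. The article names its source, the percentages in each arm, and that source carries none of the adjustment given to the other effectiveness comparisons in the section. Baseline SPADI is likely to predict whether a person is at 20 or lower later. If one arm's services happen to enrol, or selectively enrol, people with milder pain, that arm's percentage rises without any intervention effect. The primary model corrects for measured baseline SPADI; the NNT rule does not. The same report could then carry an adjusted mean difference and an NNT that point to different sizes of benefit, and the NNT is the figure readers find easier to quote.

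**Working it through.** The article gives no NNT and no recovery rate, so there is no stated figure to reproduce. The check asks how far chance baseline imbalance could move a crude NNT.

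**Stated inputs.** 832 participants, 416 per arm, 16 services; effect 0.30 SD; SD 24 to 30; ICC 0.02; 25% loss to follow-up. Hence 832/16 = 52 enrolled and 52 × 0.75 = 39 retained per service.

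**Assumed inputs.** The ICC and SD, given for the sample size, also apply to baseline SPADI. Control percentage at 20 or lower is 40% (range 30 to 50%). Baseline-outcome correlation is 0.5 (also 0.7). A normal SPADI scale is cut at the threshold.

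A correlation of 0.5 is compatible with the sample size but not fixed by it. The unclustered requirement is 234 per arm; 234 × 1.76 / 0.75 = 549, and 549 × (1 − 0.5²) = 412, close to the stated 416. A correlation of 0.6 with the design effect for 52 per service gives 404, so other values fit too.

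**1. Chance baseline difference between arms**

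- Design effect at baseline: 1 + (52 − 1) × 0.02 = 2.02
- SD of the difference, in SD units: √(2 × 2.02 / 416) = 0.0985
- In SPADI points: 0.0985 × 24 = 2.4 and 0.0985 × 30 = 3.0, against a target difference of 8 to 10

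**2. Expected NNT with no imbalance**

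- Intervention percentage: Φ(z(0.40) + 0.30) = Φ(−0.253 + 0.30) = 0.519
- Risk difference: 0.519 − 0.400 = 0.119
- NNT: 1/0.1186 = 8.4 (9.0 at 30% control recovery, 8.5 at 50%)

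**3. Crude NNT under chance imbalance**

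The imbalance shifts the outcome contrast by correlation × k × 0.0985 SD, where k is the number of SDs of imbalance. At correlation 0.5 and k = 1.96 the shift is 0.5 × 1.96 × 0.0985 = 0.097.

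- Favouring the intervention: Φ(−0.253 + 0.30 + 0.097) − 0.40 = 0.157, NNT 6.4
- Favouring control: Φ(−0.253 + 0.30 − 0.097) − 0.40 = 0.080, NNT 12.5

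| Control recovery | Correlation | k = 1 | k = 1.96 |
|---|---|---|---|
| 40% | 0.5 | 7.2 to 10.1 | 6.4 to 12.5 |
| 40% | 0.7 | 6.8 to 11.0 | 5.8 to 15.5 |
| 30% | 0.5 | 7.7 to 10.8 | 6.7 to 13.5 |
| 50% | 0.5 | 7.3 to 10.1 | 6.5 to 12.4 |

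**4. Interval, only if one is given**

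Applying ICC 0.02 to the binary outcome (an assumption) with 39 retained per service, the design effect is 1 + 38 × 0.02 = 1.76 and √1.76 = 1.327. An interval on the risk difference from raw counts would be 1 − 1/1.327 = 25% too narrow. At 40% control recovery and 312 retained per arm (416 × 0.75), the 95% limits for the NNT are 5.1 to 24 ignoring clustering and 4.5 to 64 allowing for it. Clustering hardly moves the point estimate.

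**The case against.** The strongest defence is that this is a descriptive supplement. It follows the mean difference and standardised effect size, is not a listed outcome, and drives no test, sample size or pilot criterion. Arm percentages with an NNT are conventional, and chance imbalance makes a crude randomised contrast imprecise rather than biased. This stands and limits the severity. It does not remove the point: an avoidable loss of precision of this size matters for an effect measure with 8 services per arm, and differential recruitment, which the article itself raises, would be bias and not chance.

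Three stronger readings are tempting, and the article does not support them.

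- **That the NNT interval will be too narrow.** No interval is specified, so the 25% figure is conditional on someone computing one from raw counts.
- **That only responders are counted and missing data are ignored.** The primary model is described as "using available data from all time points and assuming missing data are random"; for the NNT step neither denominator nor missing-data rule is stated. Both may properly sit in the statistical analysis plan, which is not shown.
- **That people already at 20 or lower at entry distort the NNT.** Eligibility sets no SPADI minimum: people "aged 18 years or over presenting with shoulder pain will be invited to participate". But the phrase "to score 20 or lower on the SPADI, indicating recovery" describes predicted scores at baseline, while the NNT sentence refers only to a state at follow-up. If such people are balanced between arms and contribute equally, they mainly dilute the contrast: for an assumed share of 5 to 15%, the NNT among the rest is 8.0 to 7.2 instead of 8.4.

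**Conclusion.** The point holds in a narrow form and is minor. As written, the NNT comes from unadjusted arm percentages, below the standard the same section sets for its other between-arm comparisons. Chance baseline imbalance could move it from 8.4 to anywhere between about 6.4 and 12.5 (5.8 to 15.5 at correlation 0.7), and differential recruitment could add to that. The baseline SD of 2.4 to 3.0 points rests on carrying the sample-size ICC and SD over to baseline. Every NNT value rests further on an assumed recovery rate, effect and correlation. A reader might infer that the trial's main conclusion is at risk; it is not, because the primary model already adjusts for baseline SPADI and clustering.

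**What to change.** Analyse SPADI of 20 or lower at 6 and 12 months with the mixed logistic model already planned for categorical outcomes: baseline SPADI, age, sex and service size as covariates, and service as a random effect. Standardise the fitted probabilities to a marginal risk difference at each time point and take the NNT as its reciprocal. Keep the raw numbers and percentages per arm as description only. If an interval is reported, compute it with clustering allowed for. Repeating the result among participants with a baseline SPADI above 20 is an optional supplement.

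The cost is a little extra analysis and a sentence in the plan. No new data are needed, since baseline SPADI, age, sex and service size are already collected. The adjustment deals with imbalance in these measured variables; it cannot remove differential recruitment on unmeasured ones.
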